### Baseline Assessment and Randomization

After obtaining written informed consent, a baseline (pre-treatment) assessment will be performed. Subjects will be randomized into either the intervention or the control group. A study coordinator will randomize subjects by means of a computer-generated list of random numbers in blocks of six, stratified by gender. Treatment assignments will be concealed in consecutively-numbered sealed envelopes, which will be opened sequentially upon subject enrollment. As it is a single-blind study, the subjects and the study coordinator will not be blinded to the treatment assignment. However, the study coordinator will not take outcome measurements. All investigators and outcome assessors will be blinded to the treatment assignment.

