### Primary Outcomes

#### Simplified Face Scale

A simplified face scale will be used to assess mood state before and after each session. This very brief, pictorial scale of mood uses a sequence of 7 faces and does not require reading literacy [27]. The original face scale contains 20 drawings of a single face arranged in serial order by rows, with each face depicting a slightly different mood state [42]. However, sometimes the subjects were confused by the original face scale because it contained too many similar images. Thus, the scale was simplified by using only 7 images from the original set. The 7 faces range from very happy at the left to very sad at the right.

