### Statistical Analysis

Double data entry, consistency check, and data cleaning will be performed prior to data analysis. An intention-to-treat (ITT) analysis will be carried out, in that all available data will be included, without considering the subjects’ compliance to the allocated treatment. Mean and standard deviation will be used for continuous variables while frequency and percentage will be used to describe the distribution of ordinal and categorical variables. Unpaired tests will be used for the primary analysis. Differences between the intervention and control groups in relation to outcome measures will be compared using an analysis of variance (ANOVA) or independent *t* tests. In order to increase precision in estimating the effect of interest, the analysis of covariance (ANCOVA) will be used to take into account the possible confounding effects of the covariates, such as age, education, etc. A mixed-model, repeated-measures ANCOVA will be used to compare the reactions towards each treatment captured by the observation table in both groups. The effect size will be computed to show the magnitude and direction of the effect of the intervention group relative to the control condition for each outcome variable. Data analyses will be conducted by SPSS Statistics software. A *P*<.05 will be taken as the level of statistical significance. The 95% confidence interval around the differences will be calculated.

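### The primary test is unadjusted, and no model names the outcome's starting value or the gender stratum, which costs precision in a trial sized at 15 evaluable subjects per arm

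*Protocol article*

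**What the plan says.** Under Statistical Analysis, the protocol article states: "Unpaired tests will be used for the primary analysis". Group differences "will be compared using an analysis of variance (ANOVA) or independent" t tests. It does not say whether the response is the post-treatment value or the change.

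A second, adjusted analysis follows: "In order to increase precision in estimating the effect of interest, the analysis of covariance (ANCOVA) will be used", so as to "take into account the possible confounding effects of the covariates, such as age, education, etc". The observation table has its own model: "A mixed-model, repeated-measures ANCOVA will be used to compare the reactions towards each treatment captured by the observation table in both groups". No covariates are named for it.

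Two design facts bear on this:

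- **Stratum.** Under Baseline Assessment and Randomization, subjects are allocated "by means of a computer-generated list of random numbers in blocks of six, stratified by gender".
- **Starting values.** Table 1 schedules MMSE at screening and post-treatment, and CSDD and ZBI at pre- and post-treatment. The Simplified Face Scale section adds: "A simplified face scale will be used to assess mood state before and after each session". The observation table is scored from session videos and has no pre-treatment value.

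**The concern.** The outcome's own starting value is usually the strongest predictor of its later value, and a stratification factor is normally carried into the model. The plan names neither. It names age and education instead, and it places even that adjustment outside the test called primary.

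The trial expects 15 evaluable subjects per arm, so precision is scarce and chance imbalance in starting values can be appreciable. Leaving out a prognostic stratum also keeps between-gender variation in the error term, although the design has already balanced it across the arms. Finally, a t test or ANOVA plus an ANCOVA with an open covariate list allows more than one P value for the same question.

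**Working it through.** **Inputs.** From Sample Size Calculation: pilot face-scale change 0.63, SD 0.74, alpha .05, power .9, 15 per group, 25% attrition, 40 in total. Assumed, because the article gives neither: pre-post correlation r of 0.3 to 0.7, and a share of outcome variance due to gender of 0 to 20%. Also assumed: a two-sided test, 1:1 allocation, equal pre and post SDs, and one pre and one post value per subject.

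**Step 1: the plan's own figure.** The standardised change is 0.63/0.74 = 0.851. The one-sample normal approximation gives ((1.960 + 1.282)/0.851)² = 14.5, so 15. Allowing for attrition, 15/0.75 = 20 per arm, or 40 in total. The stated numbers reproduce, but for a within-group change. The steps below take 0.63 as the between-arm difference.

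**Step 2: three ways to compare the arms.** The SD of 0.74 belongs to the change, so:

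- SD of change = 0.74
- SD of post score = 0.74/√(2(1−r))
- ANCOVA residual SD = SD of post score × √(1−r²)

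The ANCOVA error variance is therefore (1−r²) of the post-score variance and (1+r)/2 of the change-score variance. Power comes from the noncentral t distribution with noncentrality (0.63/SD)√(15/2), on 28 degrees of freedom (27 for ANCOVA).

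| r | SD post | SD ANCOVA | Power, change | Power, post | Power, ANCOVA |
|---|---|---|---|---|---|
| 0.3 | 0.625 | 0.597 | 61% | 76% | 80% |
| 0.5 | 0.740 | 0.641 | 61% | 61% | 74% |
| 0.7 | 0.955 | 0.682 | 61% | 41% | 68% |

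By the normal approximation, 90% power needs 29 per arm on change; 21, 29 and 49 on post scores; and 19, 22 and 25 with ANCOVA. Adding gender takes one more degree of freedom and about 0.1 point of power if gender is not prognostic.

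These ANCOVA figures ignore chance imbalance in the starting value, which on average multiplies the variance by about 1 + 1/(2×15 − 4) = 1.04. Dividing the standardised effect by √1.04 lowers them to about 78%, 72% and 67%. The ordering is unchanged.

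**Step 3: leaving out gender.** This was simulated with 8,000 runs per setting: 30 subjects, an assumed 18 women and 12 men, complete blocks of six within gender, and a standardised difference of 0.851.

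| Variance due to gender | Type I error, unadjusted | Type I error, adjusted | Power, unadjusted | Power, adjusted |
|---|---|---|---|---|
| 0% | 0.051 | 0.052 | 61% | 61% |
| 5% | 0.044 | 0.051 | 61% | 63% |
| 10% | 0.039 | 0.049 | 62% | 66% |
| 20% | 0.027 | 0.049 | 62% | 71% |

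The complete blocks make gender balance exact. With dropout the balance loosens, and the conservatism would be somewhat weaker.

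**The case against.** **The covariate list is open.** It is introduced by way of example and ends in etc., so neither starting value nor gender is excluded. A t test on change, the quantity used to size the trial, would use the starting value. A reader might infer that collected information is thrown away; the article does not establish that. What stands is that neither variable is named, and that a change-score test is less efficient than ANCOVA at every correlation examined.

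**Precision is already an aim.** A reader might take the ANCOVA to be justified by confounding alone, but the same sentence opens with precision as its purpose. That is a fair defence of the intent. It does not explain why the named covariates leave out the likely strongest predictor, or why the adjusted model is not the primary one.

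**Not every primary outcome is affected alike.** The observation table has no starting value and is assigned a mixed-model ANCOVA. Only the gender part of the point applies there.

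**The face-scale baseline is not clean.** Table 1 has no face-scale entry in its pre-treatment column. Every before-session score follows randomisation in unblinded subjects, and those from session 2 onward also follow treatment. This objection stands, and it limits the covariate to the score before session 1.

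**Detail may lie in an analysis plan that is not shown.** True of a full covariate list. The point here concerns what the article does fix: an unadjusted primary test.

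**Conclusion.** The point holds as one of efficiency. At 15 per arm, ANCOVA on the starting value gains about 4, 12 and 27 points of power over a post-score t test, and about 18, 12 and 7 points over a change-score t test, at correlations of 0.3, 0.5 and 0.7. Adding gender gains 0 to about 9 points if gender explains 0 to 20% of the variance. These sizes rest on the assumed ranges and on reading the pilot change as a between-arm difference; nothing in the article shows that gender predicts outcome.

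Two stronger readings are not supported:

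- A reader might conclude that ignoring the stratum invalidates the test. In the simulation type I error stays at or below about 0.05, so the test is conservative rather than invalid.
- A reader might divide 0.851 by √(1−r²) and expect power of 66%, 74% and 88%. That treats the SD of change as the SD of a post score. With the SDs kept consistent, ANCOVA power falls from 80% to 68% as r rises, and its advantage over the change-score test narrows.

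**What to change.** Make one model primary for each outcome, with arm, gender and the pre-treatment value of the same outcome:

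- **Face scale:** the score before session 1, not later before-session scores. State that it is taken after randomisation but before any treatment.
- **MMSE:** the screening score.
- **CSDD and ZBI:** the pre-treatment scores.
- **Observation table:** no starting value exists, so include gender in the planned mixed model.

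Report the unadjusted test and the age/education-adjusted ANCOVA as sensitivity analyses, with the covariate list closed.

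The change is to the analysis text. It needs no extra subjects or measurements and costs two degrees of freedom (one for the observation table).

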**Methods:**

For the study, 40 community-dwelling older Chinese adults (≥60 years) with mild to moderate dementia will be recruited and randomly assigned to the PARO therapy group or the psychosocial activities control group. Both treatments consist of six, 30-minute weekly sessions, which will be conducted in a geriatric day hospital. Subjects in both groups will be assessed by a trained research assistant at baseline (pre-), during, and post-treatment. Mood (assessed with a simplified face scale), social interaction, and communication (ie, facial expressions and reactions towards each treatment, assessed with an observation table) will be the primary outcome measures. Secondary outcome measures will include assessments on cognitive function (Mini-Mental State Examination) and depressive symptoms (Cornell Scale for Depression in Dementia), as well as caregiver burden (Zarit Burden Inventory). Subjective impression towards each treatment and qualitative comments from the caregivers, facilitator, and therapists will also be obtained.

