### Outcome Measures

Measurement of outcomes will take place at pre-, during, and post-treatment. Mood, social interaction, and communication (ie, facial expressions and reactions towards each treatment) will be the primary outcome measures. Secondary outcome measures will include cognitive function and depressive symptoms, as well as caregiver burden. Pre-treatment and post-treatment assessments will be administered by a trained research assistant who will remain blinded to group allocation. Outcome measures administered at each time point are described in Table 1. Attendance at each session will be recorded for all subjects in the study.

**Table 1 table1:** Schedule of assessments.

Assessments	Screening	Pre-treatment	Treatment session number						Post-treatment
			1	2	3	4	5	6	
MMSE^a^	√ ^g^								√
CDR^b^	√								
CMAI^c^	√								
Demographics, lifestyle, and social characteristics		√							
Simplified face scale			√	√	√	√	√	√	
Observation table^d^			√	√	√	√	√	√	
CSDD^e^		√							√
ZBI^f^		√							√
Subjective impression questionnaire			√	√	√	√	√	√	
Qualitative comments from caregivers, facilitator, and therapists									√

^a^Mini-Mental State Examination (MMSE)

^b^Clinical Dementia Rating (CDR)

^c^Cohen-Mansfield Agitation Inventory (CMAI)

^d^Facial expressions and reactions towards each treatment

^e^Cornell Scale for Depression in Dementia (CSDD)

^f^Zarit burden interview (ZBI)

^g^The √ indicates at which point of the study the respective assessments will take place.

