### Sample Size Calculation

Sample size calculations were based on the effects on mood in the pilot study: a sample size of 15 subjects per group will allow us to detect differences among the mean values of face scale scores (0.63, SD 0.74) between pre- and post-interventions using one sample *t* test (alpha=.05 and power=.9). Given that the attrition rate of 20% was observed in a previous PARO study of people with dementia [30], we will estimate a more conservative attrition rate of 25%, and thus we will recruit a total of 40 subjects.

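### Mood is scored at all six sessions, but the repeated-measures model is named only for the observation table and no summary of the 12 mood readings is given for the unpaired test

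*Protocol article*

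**What the plan says.** The Outcome Measures section makes mood primary: "Mood, social interaction, and communication (ie, facial expressions and reactions towards each treatment) will be the primary outcome measures". The Simplified Face Scale section sets the timing: "A simplified face scale will be used to assess mood state before and after each session". The abstract gives the number of sessions: "Both treatments consist of six, 30-minute weekly sessions". Table 1 agrees: it ticks the face scale at sessions 1 to 6 and shows no reading in the separate pre-treatment and post-treatment columns. The observation table has the same six ticks.

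The Sample Size Calculation section rests on this outcome: "Sample size calculations were based on the effects on mood in the pilot study". It uses one mean change and one SD, "face scale scores (0.63, SD 0.74) between pre- and post-interventions", with "alpha=.05 and power=.9".

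The Statistical Analysis section makes the primary analysis unpaired and says that group differences in the outcome measures "will be compared using an analysis of variance (ANOVA) or independent *t* tests". ANCOVA is added for covariates, with age and education as examples. The repeated-measures model comes next, for one outcome: "A mixed-model, repeated-measures ANCOVA will be used to compare the reactions towards each treatment captured by the observation table in both groups". The section also says that the intention-to-treat analysis will include all available data.

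**The concern.** Two primary outcomes share one six-session schedule. One gets a model built for repeated measurements; the other, which drives the sample size, gets a method that takes one number per subject, and that number is not defined. The protocol does choose a method for mood, so this is more than a detail left for later: the method does not match the way mood is collected.

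Two things are at stake. The first is precision: if the number tested is a single pre-post change, most mood readings do not contribute, in a trial of 40 subjects. The second is the question being answered. The sample-size wording can mean the change within a session or the change from the first session to the last. The first is an immediate response to a session; the second is a shift in mood over six weeks.

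**Working it through.** **Inputs from the protocol.** Six sessions with two readings each: 6 × 2 = 12 face-scale scores per subject. Mean change 0.63, SD 0.74, alpha 0.05, power 0.90, 15 per group before attrition, attrition 25%, 40 in total. Sidedness is not stated; two-sided is assumed.

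**The plan's own figure.** One-sample normal approximation:

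n = (SD × (z₀.₉₇₅ + z₀.₉₀) / change)² = (0.74 × 3.2415 / 0.63)² = 14.50, rounded up to 15.

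Attrition: 15 / 0.75 = 20 per group, 40 in total. Both figures reproduce. The calculation uses one change per subject.

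**Assumptions for the illustration.** None of these is in the protocol:
- 0.63 is the difference between arms, so the control arm does not change;
- 0.74 is the SD of one session's change, in both arms;
- the effect is the same at every session;
- the changes of one subject at different sessions have a common correlation ρ, shown as a range;
- 15 per arm, all six sessions attended.

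**One change per subject, two-sample t test.** Noncentrality = 0.63 / (0.74 × √(2/15)) = 2.33 on 28 degrees of freedom; power is 0.61.

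**Mean of six changes per subject, two-sample t test.** The variance is multiplied by (1 + 5ρ)/6, so SD = 0.74 × √((1 + 5ρ)/6).

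| ρ (assumed) | Variance factor | SD of mean | Power, 15 per arm |
|---|---|---|---|
| 0.3 | 0.417 | 0.478 | 0.94 |
| 0.5 | 0.583 | 0.565 | 0.84 |
| 0.7 | 0.750 | 0.641 | 0.74 |

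At ρ = 0.8 power is 0.69. The variance factor is below 1 for every ρ below 1, so under these assumptions averaging always helps; how much depends on ρ.

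**Sensitivity to the zero-change assumption.** The control arm receives table games in groups, so it may improve too. If the difference between arms were half as large (0.315), power would be 0.20 for one change and 0.41, 0.31 or 0.26 for the mean of six at ρ = 0.3, 0.5 or 0.7. The order stays the same; the levels do not.

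**What missed sessions do.** For k attended sessions the variance factor is (1 + (k − 1)ρ)/k. At ρ = 0.5 it is 0.583 for six sessions and (1 + 0.5)/2 = 0.75 for two. A t test on subject means gives both subjects the same weight; a mixed model weights them by the information they carry and allows for which sessions were attended.

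**The case against.** The strongest reply is that a t test is not wrong here. Averaging each subject's six within-session changes and comparing the means by an independent t test or ANCOVA fits the stated methods, is valid, and with complete data estimates the same average effect as a mixed model. This stands. The power gain shown above comes from averaging, not from the mixed model, whose own advantage lies in incomplete attendance.

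It also stands that the illustration is soft. If 0.63 and 0.74 were already averages over sessions, or were first-to-last changes, the comparison with 61% would not apply. The figures are for within-session change, whereas the model proposed below analyses the post-session score adjusted for the first reading, whose SD the protocol does not give.

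Three stronger readings are tempting and are not supported:
- A reader might infer that six changes per subject will be entered as independent rows, which would raise the type I error (to about 30% at ρ = 0.5, from 2 × (1 − Φ(1.96/√3.5))). No section proposes this, and the authors use a repeated-measures model for the other per-session outcome.
- A reader might infer a last-session test on about 30 of the 40 subjects. No such test is stated, and the commitment to all available data points away from it.
- A reader might suppose that a mixed model would use everyone randomised. A subject who attends no session has no mood score to contribute.

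Finally, this is a condensed article, and the choice of summary could sit in a fuller document. That covers the missing detail. It does not explain why the published analysis section names its repeated-measures model for one of two primary outcomes collected on the same schedule.

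**Conclusion.** The point holds as a recommended improvement in method, not as an error that invalidates the analysis. The facts are certain: 12 mood readings per subject, an unpaired method with no stated summary, and a repeated-measures model named for the observation table and not for mood. The direction is also firm: under a constant effect, using all sessions is more precise than using one change.

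Confidence in the size is low. The move from 61% to between 74% and 94% depends on assumed correlations of 0.7 down to 0.3, a constant effect, no change in the control arm, 15 per arm with full attendance, and 0.74 being the SD of one session change. It should be cited only as an illustration. With 25% attrition planned, incomplete attendance is foreseeable, and that is the main reason to prefer the mixed model to a t test on subject means.

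**What to change.** In the Statistical Analysis section, extend the mixed-model repeated-measures ANCOVA to the face scale:
- outcome: post-session score at sessions 1 to 6;
- fixed effects: arm, session, arm-by-session, the first pre-session face score, and gender (the randomisation stratum);
- random effect: subject;
- one prespecified mood contrast, for example the arm difference averaged over the six sessions, with the session 6 difference as secondary.

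If a simpler analysis is preferred, name one summary per subject for the t test or ANCOVA and say how missed sessions enter it.

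In the Sample Size Calculation section, state whether the change of 0.63 (SD 0.74) is within a session or from first to last session.

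The cost is analysis wording; no new data or software are needed. The downside is that if the effect builds over the weeks, the six-session average will be smaller than the session 6 effect, which would still be reported.

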## Results

Recruitment to the pilot study began in 2014 and the last subject is expected to complete the post-treatment assessment in 2015.

## Discussion

### Significance of the Study

The proposed study is, to our knowledge, the first RCT of the use of PARO in improving mood, and stimulating social interaction and communication compared to psychosocial activities in older Chinese adults with mild to moderate dementia in a day care setting in Hong Kong. The results could have particular importance given the rise in the prevalence of dementia in our society.

### Study Strengths and Limitations

The proposed study has several notable methodological strengths. The use of videotaped observations will allow us to capture subjects’ facial expressions and reactions towards each treatment during the treatment sessions, of which standard questionnaires or proxy interviews may miss. The modified observation table assesses the degree to which people with dementia will respond with the treatment by videotaped observation, which has the advantage in that ratings were specifically developed in the context of social interaction and communication between elderly patients with dementia and PARO or the psychosocial activities and other subjects, the facilitator, and therapists. Inter-rater and intra-rater reliabilities of the table have been developed. Another strength of the proposal is the measurement of various variables including caregiver burden, and qualitative components from the caregivers, facilitator, and therapists, which could reflect mood and social behaviours in another perspective.

There are several limitations in the protocol. Although behavioural and psychological symptoms of dementia occur frequently in people with dementia, we will confine our study population to mild to moderate dementia, and will exclude those with behavioural and psychological symptoms of dementia, limiting the generalizability of the results to a wider population. It has been suggested that interventions for those with behavioural and psychological symptoms of dementia should tailor the person’s specific needs and capabilities [50]. As such, an individual-based setting may be more appropriate to those with behavioural and psychological symptoms of dementia, while a group-based setting is preferred to examine the use of PARO in stimulating social interaction and communication. Moreover, subjects will be recruited through clinical referrals from community day care centres, clinics, and day hospitals; they may not represent all older adults with dementia in the community. In addition, the simplified face scale, CSDD, ZBI, and the subject impression questionnaire are self-reported. Misreporting and non-reporting may occur.

